### Informed consent and randomization protocol

All recalled women announced at one of the participating centers will be contacted for study participation. Written informed consent will be obtained and the first EQ-5D-5 L and STAI questionnaires regarding anxiety and current health state will be completed before any other study procedure is carried out. Participants are also asked for their consent to use their data in possible future studies. See Additional file 1 for the informed consent form in Dutch.

Women will be randomized to undergo standard of care (control arm) or CESM (intervention arm). Minimization with stratification factors will be applied in the computer-generated randomization screening and enrollment application software ALEA (version 3.0.2083.212r; ALEA Clinical, Abcoude, the Netherlands). Randomization will be stratified by the following: predominant reason for recall (mass, calcifications, asymmetry, architectural distortion), recall BI-RADS score (BI-RADS 0 versus BI-RADS 4/5), and study center. Enrollment in the four centers, including the master randomization file, will be overseen by the Study Coordinator. During the inclusion visit, written consent will be conducted and data entry will be done by one of the research team members in each center to execute randomization using ALEA. Should a problem occur in including a patient or randomization, the Study Coordinator must be reached so that he can provide assistance. After allocation, patient and radiologist will be informed about the outcome; hence, they are not blinded. However, the radiologist is blinded for the outcomes between the two groups, since the final diagnosis and pathology are not yet known. The outcome assessors and data analysts are blinded for the judgment of the next screening round by the screening radiologists, since accuracy also depends on the next screening round outcome. Each participant is assigned a trial identification number for anonymization, to analyze the data, and further to be used in publications. In each participant’s hospital patient file a statement will be noted about study participation and the assigned intervention or control group. On request, study participation can be ended during the follow-up phase.

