### Sample size calculation

Prior research showed a specificity of FFDM of 40% in this population [5]. To enable detection of a clinically relevant increase of specificity by 15% (from 40% to 55%), 176 patients without malignant disease per group are required (power 80%, alpha = 5%). The prevalence of malignant lesions in women recalled from the breast screening program is about 30%; thus, 70% have benign lesions. Therefore, a total of 251 women per group (176/0.7) has to be included. To account for 5% loss to follow-up, the final number of patients to be included is 528 (502/0.95). The calculations were done with OpenEpi [20].

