### Statistical analysis

The primary objective of the study is to demonstrate that the use of CESM as a work-up tool for women recalled from breast cancer screening is more accurate compared to standard care consisting of conventional imaging. The secondary objectives are to evaluate whether this novel approach is a more patient-friendly and cost-effective strategy in the work-up of women recalled from breast cancer screening, requiring fewer days until final diagnosis and less additional imaging.

Radiologists will prospectively provide a single BI-RADS classification for each exam, where a BI-RADS score of 1–3 will be considered ”benign” and 4-5 ”malignant”. Based on this cutoff, the final BI-RADS score and recall BI-RADS score, the diagnostic performance parameters sensitivity, specificity, PPV, NPV, and AUC under the ROC curve will be assessed as the primary endpoint for both study arms. Differences in proportions between the two randomized groups will be tested for significance with a chi-square test, and the difference in AUCs will be tested using the method proposed by Hanley et al. [21].

Secondary outcomes are QoL, patient anxiety, and cost-effectiveness. The course of scores on QoL with QALY and patient anxiety (STAI) from baseline over time at the six time points will be visualized and differences between groups will be tested using mixed linear models, which account for correlations between repeated measurements. Single and multiple imputation will be used to replace missing data.

Both intention-to-treat and per protocol analyses will be performed. The per protocol population for the primary outcomes are those who got imaging exams based on their group allocation. Women who underwent CESM in the standard care group are excluded from the per protocol analysis. For the secondary outcomes this population can be further specified to those with questionnaires completed at six time points. *P* values < 0.05 will be considered to indicate statistical significance. Analyses will be performed with SPSS (version 25, IBM Corporation, Armonk, NY, USA) and STATA (version 15, StataCorp LLC, College Station, TX, USA).

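### The primary chi-square ignores the three minimisation factors: a valid, mildly conservative test that forgoes some power if those factors predict the final reading

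*Protocol article*

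**What the plan says.** Under Informed consent and randomization protocol, the article states: "Minimization with stratification factors will be applied in the computer-generated randomization". The factors are "predominant reason for recall (mass, calcifications, asymmetry, architectural distortion), recall BI-RADS score (BI-RADS 0 versus BI-RADS 4/5), and study center": four reasons, two BI-RADS groups and, with four participating centres, four centre levels.

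Under Statistical analysis, the primary proportions are compared as follows: "Differences in proportions between the two randomized groups will be tested for significance with a chi-square test". For the ROC comparison, "the difference in AUCs will be tested using the method proposed by Hanley et al". Neither sentence names a covariate or stratum. The recall BI-RADS score appears in that section only as an input to the performance parameters. The mixed models described there are for quality of life and anxiety, and do not name the factors either.

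Sample size calculation rests on specificity: "Prior research showed a specificity of FFDM of 40% in this population". It seeks a rise to 55% with 80% power at alpha 5%, which it says needs 176 women without malignancy per group.

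**The concern.** Minimisation makes the arms more alike on its factors than simple randomisation would. If those factors predict whether a woman without cancer is read as BI-RADS 1–3, part of the chance variation in the arm difference has been removed by design. An unadjusted chi-square does not know this. Its standard error still contains the between-stratum variation, so the test rejects a little less often than 5% under the null and detects a true difference less often than an analysis that uses the factors.

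At stake is efficiency in a comparison planned close to 80% power, with information that the randomisation system already holds.

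**Working it through.** **1. The plan's own figure.** Inputs from Sample size calculation: p0 = 0.40, p1 = 0.55, d = 0.15, power 80%, alpha 5% (taken as two-sided; one-sided would give 136).

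n = [1.960·√(2·0.475·0.525) + 0.842·√(0.24 + 0.2475)]² / 0.15² = 172.8, so 173. The Kelsey formula gives 174. Both are within 3% of 176; the continuity-corrected version (186) is not. The size therefore rests on an unadjusted two-proportion test.

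Power at 176 per arm: SE under the null = √(2·0.475·0.525/176) = 0.0532; SE under the alternative = √(0.4875/176) = 0.0526; Φ[(0.15 − 1.960·0.0532)/0.0526] = 80.7%.

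**2. Analytic effect of ignoring the factors.** Let R² be the share of outcome variance among women without cancer that the factors explain, and assume full balance. The true SE shrinks by t = √(1 − R²), while the chi-square keeps the full SE.

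- Chi-square size: 2·[1 − Φ(1.960/t)]
- Unadjusted power: Φ[(0.15 − 1.960·0.0532)/(0.0526·t)]
- Adjusted power: Φ[(0.15 − 1.960·0.0532·t)/(0.0526·t)]

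| Assumed R² | Chi-square size | SE too large by | Power unadjusted | Power adjusted |
|---|---|---|---|---|
| 0 | 5.0% | 0% | 80.7% | 80.7% |
| 0.05 | 4.4% | 2.6% | 81.3% | 82.7% |
| 0.10 | 3.9% | 5.4% | 82.0% | 84.7% |
| 0.20 | 2.8% | 11.8% | 83.4% | 88.6% |

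This overstates the effect somewhat. Cancer status is unknown at allocation, so minimisation balances all women and the subset without cancer only approximately.

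**3. Simulation with that subset.** 502 women are minimised on the three factors, 30% have cancer, and specificity is tested in the rest. The pairs below are assumed control specificities for BI-RADS 0 / BI-RADS 4/5. With an assumed 70/30 mix they average about 40% (for example 0.7·46 + 0.3·26 = 40). The adjusted analysis uses arm plus main effects of the factors.

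| Assumed split | Chi-square null rejection | Chi-square power | Main-effects power | 32-cell CMH power |
|---|---|---|---|---|
| no association | 5.1% | 82.4% | 81.3% | 79.1% |
| 46 / 26 | 4.6% | 78.5% | 79.4% | 77.1% |
| 50 / 15 | 4.1% | 82.1% | 84.3% | 83.0% |
| 55 / 5 | 3.3% | 82.8% | 89.1% | 86.3% |

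Power levels carry simulation noise: with no association theory gives 80.7%. The comparison to read is within a row: −1.1, +0.9, +2.2 and +6.3 points for the main-effects model.

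A second simulation (4000 runs per setting, recall BI-RADS and reason both prognostic, linear risk-difference model with robust SE) gave unadjusted versus adjusted power as follows:

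- No association: 80.7% vs 79.7%.
- Odds ratio 2 for recall BI-RADS: 80.6% vs 80.8%.
- Odds ratio 4: 82.0% vs 84.8%.
- Odds ratio 8: 81.5% vs 86.8%.

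Chi-square null rejection was about 5% at odds ratio 2 and 4.3–4.4% at the two larger odds ratios. At odds ratio 4 and a true 15-point difference, its mean SE was 0.0526 against a true SD of 0.0511.

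**4. How many strata.** Full cross-classification has 4 × 2 × 4 = 32 cells. About 352 women without cancer give 352/32 = 11 per cell. In the table above, the 32-cell CMH keeps 0.9 of the 2.2-point gain at 50/15 and 3.5 of 6.3 at 55/5, and falls below the chi-square in the other two rows. In a separate run of 3000 trials with only recall BI-RADS prognostic, power for chi-square, CMH on recall BI-RADS alone and 32-cell CMH was 81.5 / 82.4 / 79.1% (46/26), 80.0 / 83.7 / 79.6% (50/15) and 82.5 / 89.6 / 86.3% (55/5).

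**5. Sensitivity.** 0.30 × 251 is about 75 cancers per arm. The protocol expects high sensitivity, hence few misses. A model with arm and seven factor terms (3 + 1 + 3) could then separate.

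**The case against.** The strongest reply is that nothing here is wrong. The test and the sample size agree, since both are unadjusted. The chi-square holds its level, and the stated power is met. No section reports specificity by recall BI-RADS, reason or centre, so any gain is conjecture and could be slightly negative. The article is also a condensed protocol, and an analysis plan that is not shown may add an adjusted analysis.

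Most of this stands, and it limits the point to efficiency. It does not remove it. The article names the primary test outright, nothing in it adjusts for the factors, and the sponsor thought them important enough to balance on.

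Four stronger readings are tempting and are not supported:

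- **That the primary test is invalid or raises the false-positive rate.** The error goes the other way.
- **That the chi-square leaves the trial underpowered.** Planned power already assumes this test. Whether 70% of recalled women are free of cancer is a separate question.
- **That the factors are known to be strong predictors.** Separate referral routes for BI-RADS 0 and 4/5 make this plausible for recall BI-RADS, but the protocol gives no rates. It also argues that experience in reading CESM matters little, which weakens the case for centre.
- **That the planned confidence intervals are too wide.** Statistical analysis specifies no interval for the primary proportions. The remark applies only to an unadjusted interval if one is reported.

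**Conclusion.** The allocation and the primary analysis do not match, and the consequence is modest. If the factors are prognostic, the chi-square rejects about 3.3–4.6% of the time under the null in the assumed splits, and is indistinguishable from 5% when they are weak. Power forgone is about 0 to 1 point for weak factors, 2 to 3 for strong ones and about 6 in an extreme case. If the factors are unrelated to the reading, adjustment costs about 1 point.

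These sizes rest on assumed stratum rates, an assumed 70/30 mix of BI-RADS 0 and 4/5 among women without cancer, and the planned 15-point difference. The direction depends only on the factors being prognostic. The AUC comparison also names no factors, but its size was not worked out here.

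**What to change.** - **Specificity.** Make the primary comparison a main-effects model with arm, recall BI-RADS, reason for recall and centre, reported as a standardised (marginal) risk difference with 95% CI. A CMH test with a stratified risk difference on recall BI-RADS alone is an acceptable alternative. Do not stratify over all 32 cells.
- **Sparse levels.** Fix the pooling rule for reason and centre in advance.
- **Sensitivity.** Adjust for recall BI-RADS only, or use a penalised model, to avoid separation.
- **Chi-square.** Keep it as a sensitivity analysis.

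The cost is wording in the analysis plan. No extra patients or data are needed, because the factors are recorded at randomisation. The change should be fixed before outcome data are analysed, so that it cannot look data-driven.

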### Economic evaluation

Decision-analytic modeling will be applied to estimate the cost-effectiveness of CESM compared to conventional imaging modalities FFDM or DBT for recalled women from the Dutch national screening program. The economic evaluation will be performed from both a health care and a societal perspective. Cost-effectiveness will be expressed as the incremental costs per QALY gained as outcome measure [22]. All resource use related to diagnostics will be registered. In addition, productivity loss will be measured with the iMTA Productivity Costs Questionnaire (iPCQ) at 4 weeks and at 6, 12, and 18 months [23]. Reference prices will be obtained from the Dutch manual for costing research, hospital financial department, or the literature [24]. Uncertainty surrounding the incremental costs per QALY will be analyzed with a non-parametric bootstrap analysis [25]. Results of the bootstrap analysis will be presented in cost-effectiveness planes and acceptability curves. A probabilistic sensitivity analysis will be performed to examine different parameter uncertainties.

In Fig. 4 an overview, according to Standard Protocol Items: Recommendations for Interventional Trials (SPIRIT), is given of all study activities, including the iPCQ assessments.

**Fig. 4 Fig4:**
[figure not shown]
Schedule of study activities according to Standard Protocol Items: Recommendations for Interventional Trials (SPIRIT)

## Discussion

We present the rationale and design of the RACER study, which is a multicenter, prospective, randomized controlled trial investigating the work-up after breast cancer screening referral. This design is in accordance with the SPIRIT guidelines (Additional file 2).

Recent studies have consistently shown that CESM is superior to FFDM, even when the latter is combined with targeted US [26–29]. Lobbes et al. showed that in women recalled from screening, the detection of breast cancer was comparable between the two techniques, but specificity almost doubled from 42.0 to 87.7% when using CESM as a work-up tool [3]. In other words, fewer false positive findings were observed, and with the high negative predictive value of 97.1% in this study, there was a high ability to rule out breast cancer if the CESM showed a negative exam. These initial findings were later confirmed by Lalji et al. in 199 new cases, analyzed by a panel of ten different radiologists [5]. In this study, radiologists without any CESM experience (but with extensive experience in reading FFDM exams) performed as well as radiologists with CESM experience. Reading a CESM exam does not require a dedicated learning curve. Radiologists in the participating centers will have different levels of experience in reading CESM exams. However, these works used a retrospective study design. Also, many other studies on CESM are retrospective in nature. Only some studies collect data prospectively, and most have not done so in a randomized controlled trial like the RACER study.

The RACER study has several strengths. First, a direct comparison between CESM and FFDM, both with targeted US allowed, is possible. Until now, some studies have investigated the comparison between CESM versus FFDM plus targeted US [27, 28]. However, in clinical practice, suspicious findings on CESM are further evaluated with US as well. Klang et al. recently showed that in BI-RADS 3 lesions detected on CESM, targeted US could be used to determine the necessity to perform tissue sampling [30]. Although CESM is superior to FFDM plus US, the difference in diagnostic accuracy is expected to increase again when CESM/US is compared with FFDM/US. To the best of our knowledge, this has not been studied before in a prospective study design.

Second, the patients’ mental state during the recall and diagnostic work-up is thoroughly assessed by validated questionnaires. Due to the higher diagnostic performance of CESM, especially in terms of reducing the number of false positive findings, it is expected that in the intervention arm fewer additional exams will be performed, such as follow-up after 6 or 12 months, or breast MRI. These additional exams cause a delay in the assessment of final diagnosis and increase health care costs; plus we hypothesize that this will influence a patient’s mental state during these months. Finally, the study design allows for a cost-effectiveness analysis, showing us the impact on health care costs of both strategies during this period. We hypothesize that using CESM as a work-up tool is more efficient and cost-effective than following current standard care. If proven to be cost-effective, an important hurdle is taken toward acquiring reimbursement by health insurance companies for CESM, which at present frustrates the further introduction of CESM worldwide.

Using CESM as a work-up tool also has some limitations. The most important disadvantages are the increased radiation dose and the administration of iodine-based contrast agents. Regarding the increase in radiation dose, several studies have shown that the mean radiation dose of CESM per exposure is in the range of 2.5-2.8 mGy [18, 31–33]. In comparison, the radiation dose of FFDM in these studies varied from 1.4 to 1.8 mGy. Jeukens et al. showed that the CESM radiation dose is approximately 80% higher than that in FFDM: 2.8 mGy versus 1.6 mGy, respectively [18]. Nevertheless, it is still within internationally accepted limits and does not substantially increase breast cancer incidence or mortality in women recalled from screening, who are at least 50 years. We believe that this increased dose is justified in the dedicated population as outlined. The chance of acquiring breast cancer due to this radiation exposure is expressed in the life attributable risk (LAR) numbers. For example, for a single view CESM acquisition having a mean radiation dose of 2.8 mGy per exposure, the LAR number for cancer incidence is 0.4 in 100,000 persons at the age of 60 years [34]. The LAR number for cancer mortality at this age is even 2–3 times lower. Some even advocate that there is no effect of radiation under a dose of 100 mSv. Hence, one may conclude that CESM exposure poses only a small additional risk compared to the lifetime risk for breast cancer incidence and mortality of 12,000 and 3000 cases per 100,000 women, respectively.

Regarding the use of iodine-based contrast, Houben et al. had in clinical practice in a similar population a low incidence (0.6%) of adverse hypersensitivity reactions [10]. In contrast, they also showed that occult cancers are being detected in 3–4% of the recalled women by using CESM. Consequently, the chance of finding occult (small) breast cancers is higher than the chance of having adverse reactions to contrast administrations (which are all documented in the RACER study), which in our opinion would justify the use of a CESM-based work-up of women recalled from screening.

In short, we believe that the prospective multicenter randomized controlled RACER study will show that in recalled women a work-up based on CESM will be more accurate than usual care (based on conventional imaging such as FFDM). Higher specificity at similar sensitivity will reduce false positives and the volumes of additional diagnostic exams required to reach a final diagnosis, ultimately leading to a decrease in health care costs and patient-experienced anxiety during this period.

### Trial status

Participants are currently enrolled via protocol version number 6.1 (April 23rd 2019). The study protocol was approved by the Medical Ethics Review Committee of Maastricht University Medical Center+ in January 2018. The first participants were randomized in April 2018. Enrollment is expected to be completed before January 1st, 2021.

## Data Availability

The database, once the project has ended, will be shared on request and after approval by the study committee. A part of the collected imaging and clinical data, for which the patients will explicitly give informed consent, will be shared with The D-Lab: Decision Support for Precision Medicine (GROW School for Oncology and Developmental Biology, Maastricht University Medical Center) to be used in an additional artificial Intelligence analysis.

## Abbreviations

AUC: Area under the curve
BI-RADS: Breast Imaging Reporting and Data System
CC: Cranio-caudal
CESM: Contrast-enhanced spectral mammography
CNB: Core needle biopsy
CTCM: Clinical Trial Center Maastricht
DBT: Digital breast tomosynthesis
DCIS: Ductal carcinoma in situ
eCRF: Electronic case report form
FFDM: Full-field digital mammography
FN: False negative (findings)
FNAC: Fine-needle aspiration cytology
GP: General physician
*i*PCQ: iMTA Productivity Costs Questionnaire
LAR: Life attributable risk
MLO: Mediolateral oblique
MRI: Magnetic resonance imaging
NPV: Negative predictive value
PPV: Positive predictive value
QALY: Quality-adjusted life year
QoL: Quality of life
ROC: Receiver operating characteristics (curve)
STAI: State Trait Anxiety Inventory
TN: True negative findings
TP: True positive
US: Ultrasound
VAB: Vacuum-assisted biopsy
